## Abstract

**Background::**

Cemented hip arthroplasty requires applying a layer of polymethylmethacrylate (cement) in the space between the bone and the prosthetic stem. This can be achieved using 2 techniques: the thick-layer technique (requires a layer of at least 2 mm to surround an undersized prosthetic stem), and the thin-layer technique (requires a thin layer of cement, so that the prosthetic stem fills the femoral medullary canal). Both approaches have excellent long-term clinical and radiological outcomes, although an implant's insertion into the bone generates inevitable bone mass and bone metabolic changes around it. Combination of single photon emission computed tomography and computed tomography scan (SPECT-CT) imaging combines the single photon emission computed tomography's ability to provide detailed bone metabolism assessment with the computed tomography scan's capacity to provide a meticulous anatomical study.

**Methods::**

This is a single center, open label, randomized clinical trial, performed in the premises of the Bellvitge University Hospital. Participants will be randomly assigned to the Thick-layer technique group (Exeter V40 Cemented Femoral Stem) or to the French paradox technique group (Müller Straight Stem). All participants will have a SPECT-CT scan study at 3, 6, 12, and 24 months after the surgery.

**Discussion::**

Surgical distress itself and the implant's insertion into the bone may cause microvascular changes that alter periprosthetic bone mass and bone metabolism. To the best of our knowledge, there are no studies using SPECT-CT to compare bone metabolism evolution in the postoperative period between these 2 surgical cementation techniques. We aim to provide information in this regard that could help decision making in complicated implant cases and, maybe, pave the way for larger, and methodologically improved studies.

**Trial registration::**

NCT05010733 (August 18, 2021).

## Introduction

1

### Background and rationale

1.1

Since its introduction by John Charnley in 1959, total hip arthroplasty (THA) has been one of the most successful techniques in orthopedic surgery. Total hip replacement has progressively grown, reaching figures of a million arthroplasties implanted annually worldwide.^[1]^

Technically, the components of a total hip arthroplasty, which consist of an acetabular cup and of a femoral stem, can be attached to the bone through a cemented technique or a non-cemented technique. On the cemented hip arthroplasty, attachment of the prosthesis to the bone is done by using a cement (polymethylmethacrylate) that immediately stabilizes the implanted component. On the non-cemented hip arthroplasty, the prosthetic component is attached to the bone primarily under pressure (for primary stability) and, over time, osteointegration (a direct, structural, and functional connection between living bone and the prosthetic surface) is established.

Regarding the indication of each technique, some studies have shown good long-term results for both, and, in many cases, it is up to the surgeon in charge to decide which one to use. However, in situations of poor bone “stock”, such as elderly and/or osteoporotic patients, the cemented hip arthroplasty seems to be the best choice.^[2]^

Since the beginning in the early 1960s, surgical techniques and prosthetic designs have evolved remarkably. Considering the prosthetic's femoral stem design, and the cement layer that must surround it and attach it to the bone, there are 2 clearly different techniques^[3]^:

**The thick-layer cement technique:** a cement layer of at least 2 millimeters (mm) surrounds a small enough (undersized) prosthetic stem to allow this layer of cement to fit between the femoral medullary canal and the prosthetic's femoral stem.**The thin-layer cement technique (also known as “The French Paradox**”**):** introduced in France in the early 1970s, this technique states that the prosthetic's femoral stem should “fill”, as much as possible, the femoral medullary canal, only requiring a thin layer of cement.

Both techniques have shown excellent long-term clinical and radiological outcomes. For this reason, the Orthopedic Surgery and Traumatology Department (OSTD) at the Bellvitge University Hospital uses both types of cemented prostheses (the Exeter V40 cemented femoral stem, for the thick-layer cement technique, and Müller Straight Stem, for the thin-layer cement technique).

Nevertheless, an implant's insertion into the bone (in this case, the femur) generates bone mass and bone metabolism changes around the implant. Monitoring these metabolic changes, and, therefore, the peri-prosthetic bone reaction, is of great importance when evaluating the results of each prosthetic model. There are many methods for peri-prosthetic bone changes monitoring, such as plain radiography, computed tomography (CT) scan, magnetic resonance imaging, dual energy radiography absorption and single photon emission computed tomography (SPECT). SPECT with technetium 99-labeled methyl-diphosphonates (MDP) is a useful tool for bone metabolism assessment^[4]^ and, although this technique may show insufficient anatomical details, its combination with CT scan (SPECT-CT) provides a solution and allows a combined metabolic and morphological study.^[5]^

To our knowledge, there are no studies comparing bone metabolism evolution in the postoperative period between these 2 approaches (thick-layer cement vs “French paradox”) with SPECT-CT. The aim of this work is to provide information on bone metabolic activity in the postoperative period of these 2 femoral stem models and to determine whether there are differences between them.

### Explanation for the choice of comparators

1.2

We will compare the 2 types of cemented stem prostheses used for THA in our clinical practice: the Exeter V40 cemented femoral stem [Stryker Orthopaedics, Mahwah, NJ], for the thick-layer cement technique, and Müller straight stem [Zimmer, Winterthur, Switzerland], for the “French paradox” technique.

### Objectives

1.3

The primary and secondary objectives are summarized in Table 1.

**Table 1 T1:** Summarized study objectives.

Primary objectives
To describe the bone metabolic activity in cemented stem prostheses.
To describe the bone morphology in cemented stem prostheses.
Secondary objectives
To estimate the alignment angle.
To estimate the axial displacement degree.
To classify radiographically the prostheses’ risk of loosening according to the Harris Radiographic Classification of Loosening Risk (see Table S5, Supplemental Digital Content).
To estimate the clinical outcomes from THA according to the Harris Hip Score (see Table S1, Supplemental Digital Content).
To estimate the clinical outcomes from THA according to the Merle d’Aubigné Score (see Table S2, Supplemental Digital Content).
To estimate the clinical outcomes from THA according to the WOMAC Index (see Table S3, Supplemental Digital Content).
To estimate quality of life according to the EuroQoL-5D-3L© questionnaire (see Table S4, Supplemental Digital Content).

### Trial design

1.4

This is a single center, randomized, controlled, pilot clinical trial in patients who undergo total hip arthroplasty surgery with implantation of a cemented prosthetic.

Those patients who accept to participate will have a plain radiography and a SPECT-CT, at 3, 6, 12, and 24 months of the intervention. These SPECT-CTs will be done in addition to the usual clinical practice complementary imaging exams and will require the administration of the ^99m^Technetium- methylene diphosphonate (^99m^Tc-MDP) radiopharmaceutical.

Since this is a study based on usual clinical practice, collection of existing information from medical records, and prospective evaluation of the SPECT-CTs, no significant risk is expected in advance for the patients enrolled. Besides, given the low doses of ^99m^Tc-MDP administered for this type of scan,^[6]^ radiation-induced adverse effects are extremely rare, especially in those over 60 years of age, which is the age-range of this study.^[7]^ However, an insurance cover will be hired, should any unforeseen problems arise because of the study.

The postoperative SPECT-CT follow-up results will be explained to each patient. After the 24-month SPECT-CT, the patients’ participation in the study will be terminated and usual clinical practice follow-up shall be provided as for the general population.

This study was registered in the ClinicalTrials.gov Protocol Registration and Results System (Identifier: NCT05010733, August 18, 2021).

## Methods: participants, interventions, and outcomes

2

### Study setting

2.1

This is a single-center clinical trial. Therefore, this study will be entirely carried out in Bellvitge University Hospital (L’Hospitalet de Llobregat, Barcelona, Spain) and will be coordinated by the OSTD. This is a fully equipped tertiary hospital.

### Eligibility criteria

2.2

#### Inclusion criteria

2.2.1

Patients ≥18 years-old, of both genders, undergoing a primary total hip arthroplasty surgery with implantation of a cemented prosthetic (Exeter V40 cemented femoral stem or Müller straight stem), with a diagnosis of hip osteoarthritis, operated by the OSTD at Bellvitge University Hospital during the 2 years after protocol's approval by the ethical committee, who have signed a written informed consent.

#### Exclusion criteria

2.2.2

Patients allergic to ^99m^Tc-MDP radiopharmaceutical; with claustrophobia; with a background of an active septic process; a postoperative septic complication; periprosthetic fracture or misalignment of the prosthetic component; or those who have a total hip prosthetic implanted due to a sub capital femoral fracture.

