### Outcomes

2.7

Study primary and secondary outcomes are summarized in Table 2.

**Table 2 T2:** Summarized primary and secondary study outcomes.

Primary outcomes
Bone metabolic activity: number of counts per image set (median and its 95% CI) in the SPECT study. *Note: Counts per image set are a measure unit defined as the number of photons captured by the gamma camera, which represent the radiopharmaceutical uptake.* *SPECT will be performed at 3, 6, 12, and 24 mo of the intervention.*
Bone morphology: Alignment angles (median and its 95% CI) in the plain radiography and in the CT scan study. *Note: Alignment angles will be measured in degrees using the anatomical axis of the femur as a reference. Stem deviations from the femoral anatomical axis will be classified as “Varus” (if the tip of the stem is situated laterally to the femoral anatomical axis) or as “Valgus” (if the tip of the stem is situated medially to the femoral anatomical axis).* *Plain radiography will be performed at baseline and at 3, 6, 12, and 24 mo of the intervention.* *CT Scan will be performed at 3, 6, 12, and 24 mo of the intervention.*
Secondary outcomes
Axial displacement (median and its 95% CI) in the plain radiography and in the CT scan study. *Note: Axial displacement will be measured (in millimeters) using the inter-teardrop line as a reference. In the CT Scan study, this inter-teardrop line will be measured on the coronal plane.* *Axial displacement will be assessed at 3, 6, 12, and 24 mo of the intervention.*
Prosthesis loosening risk: number (and proportion) of patients classified as “possibly loose”, “probably loose”, and “definitely loose”, according to the Harris Radiographic Classification of Loosening Risk. *Note: Possibly Loose: Presence of a radiolucent line of 50% to 99% of the cement-bone boundary; Probably Loose: Radiolucency line at 100% of cement-bone boundary; Definitely Loose: Stem migration or a fracture of the cement mantle.*
Clinical outcomes: Harris Hip Score (median and its 95% CI). *Note: Being a score of 100 points the best possible result, and a score of 0 the worst possible result.*
Clinical outcomes: Merle d’Aubigné Score (median and its 95% CI) *Note: Clinical grades (Very good, Good, Medium, Fair, Poor) are given by the scores of Pain and Walking ability and adjusted down 1 to 2 grades, depending on the mobility score.*

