#### Study procedure

2.7.1

Participants will be screened among patients on the waiting list for THA. The screening will be carried out following the waiting list's order (i.e., the first patient on the waiting list will be contacted first, and so on, until the last patient on the waiting list is contacted or until the planned sample size has been reached, whichever comes first). Patients will be contacted by phone by a study team member, who will explain the study to them and answer any questions that may arise. If the patient accepts to participate, a screening visit will be scheduled.

On the day of “Visit 1”, the Study Information Sheet will be delivered to the patient and any other doubts that may arise will be answered. If the patient accepts to participate, he/she will be asked to sign the Informed Consent, a *sine qua non* condition for he/she to participate in the trial. Hereafter, all the information mentioned on Table 3 will be gathered and the complementary exams will be scheduled.

**Table 3 T3:** Participant timeline.

	Visit 1	Visit 2	Visit 3	Visit 4	Visit 5	Visit 6	Visit 7
	Patient screening	Day of surgery	Hospital discharge	3 (±1 wk) mo of the surgery	6 (±2 wks) mo of the surgery	12 (±1) mo of the surgery	24 (±1) mo of the surgery
Obtaining informed consent	✓						
Eligibility criteria assessment	✓						
Demographic data	✓						
General examination (1)	✓	✓	✓	✓			
General laboratory blood tests (2)	✓		✓	✓	✓	✓	✓
Randomization		✓					
SPECT-CT				✓	✓	✓	✓
Plain radiography	✓			✓	✓	✓	✓
Clinical outcomes: Harris Hip Score, Merle d’Aubigné Score and WOMAC index score	✓			✓	✓	✓	✓
QoL questionnaire	✓			✓	✓	✓	✓
Safety: adverse events	✓	✓	✓	✓	✓	✓	✓
Concomitant treatment recording				✓	✓	✓	✓

The institutional review board (IRB) approved the protocol on May 20, 2021 (code ICPS033/20). We estimate that we will need approximately 6 months to identify the study population, establish the surgical indication, include them on the waiting list and perform the surgery. The study will be carried out between 2021 and 2024.

By the moment of submitting this manuscript, participant recruitment (patients’ screening visit) was still in progress.

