##### Sequence generation, concealment mechanism, and implementation

2.10.1.1

The principal investigator (DR) will oversee the screening procedure (i.e., contacting with patients and performing Visit 1). The randomization process will be centralized electronically using the e-CRF itself (research electronic data capture software [REDCap] platform) the day before the surgery. The randomization list will be computer-generated in blocks of 4. Patients will be assigned to the study groups at the time of enrollment on the study.

The randomization to the type of cemented stem prosthesis studied will be blinded to the participant and the surgeon team until the day of the surgery.

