### Who will obtain informed consent?

2.23

Principal investigator (or another physician from the study team) will inform the screened patients about the study and ask them to sign the written informed consent in visit 1, whether the patient is interested in participating in the study. If he/she is interested to participate, the investigator of the study team will double-check the eligibility criteria before obtaining the signed written informed consent.

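### Three exclusion criteria can be met only after randomisation, and one of them, misalignment, overlaps the primary alignment-angle outcome

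*Protocol article*

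**What the plan says.** Section 2.2.2 of the protocol article lists among its exclusions "a postoperative septic complication; periprosthetic fracture or misalignment of the prosthetic component". It gives no angle, time point or assessor for misalignment.

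The other relevant statements are these:

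- **Population (2.2.1):** patients "undergoing a primary total hip arthroplasty surgery with implantation of a cemented prosthetic", with a diagnosis of hip osteoarthritis.
- **Eligibility:** in Table 3 the row "Eligibility criteria assessment" is ticked at Visit 1 (screening) only. Section 2.23 adds that the investigator "will double-check the eligibility criteria before obtaining the signed written informed consent".
- **Randomisation (2.10.1.1):** "centralized electronically using the e-CRF itself (research electronic data capture software [REDCap] platform) the day before the surgery". Table 3 marks it on the day of surgery.
- **Primary outcome (Table 2):** "Bone morphology: Alignment angles (median and its 95% CI) in the plain radiography and in the CT scan study". The note defines the angle as the stem's varus or valgus deviation from the femoral anatomical axis, and section 2.14 analyses its median by stem type.
- **Blinding (2.10.2):** participant and surgical team know the stem after assignment; data analysts are blinded.
- **Analysis population (2.16):** the text under this heading deals with imputation only.

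**The concern.** Exclusion criteria are meant to define who may be randomised. Three of these describe events that need a prosthesis or an operation that does not yet exist when eligibility is checked. If they are used, they work as rules for removing patients after allocation.

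Misalignment matters most, because a misaligned stem is an extreme value of the angle that the trial compares. The stem that produces more misaligned implants would lose more patients, and the remaining patients would look more alike across arms. Infection and periprosthetic fracture may plausibly affect periprosthetic uptake, the other primary outcome. Because misalignment is undefined, deciding who meets it is a judgement made in an open-label setting, and blinding the analyst afterwards cannot repair that.

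**Working it through.** **Step 1: timing.** The order is eligibility at Visit 1, randomisation the day before or on the day of surgery, then implantation. A primary arthroplasty means that the study hip has no earlier prosthesis to be misaligned or fractured around, and no earlier operation on that joint to be septic after. All three criteria therefore fall after allocation for the study hip, whichever randomisation day is right.

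**Step 2: overlap with the outcome.** The criterion covers the prosthetic component, which includes the stem. The outcome is the stem's deviation from the femoral axis. The two concern the same feature, although the criterion has no numerical cut-off.

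**Step 3: numbers at risk.** Section 2.8 sets 16 patients, 8 per group, without a formal calculation, so there is no planned power or effect to reproduce. One loss is 1/8 = 12.5% of an arm. If a proportion p of patients meets one of the criteria (p is assumed; the document gives no rate), the chance of losing at least one of 16 is 1 − (1 − p)^16:

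- p = 2%: 28%
- p = 5%: 56%
- p = 10%: about 81%
- p = 20%: 97%

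**Step 4: effect on the alignment comparison.** The SD, cut-off and true difference are all assumptions. Take normal angles with the same SD σ in both arms, one arm centred at 0 and the other at 2 degrees, and exclude angles beyond ±c. For an arm centred at μ:

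- fraction excluded = 1 − [Φ((c − μ)/σ) − Φ((−c − μ)/σ)]
- retained median = μ + σ·Φ⁻¹{[Φ((c − μ)/σ) + Φ((−c − μ)/σ)]/2}

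Example with σ = 2, c = 3, μ = 2: Φ(0.5) = 0.6915 and Φ(−2.5) = 0.0062. Excluded: 1 − 0.6853 = 31%. Retained median: 2 + 2·Φ⁻¹(0.3489) = 2 + 2(−0.388) = 1.22. The arm centred at 0 keeps a median of 0, so the retained median is also the retained difference.

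| Assumed SD | Assumed cut-off | Excluded, arm at 0 | Excluded, arm at 2 | Retained difference | Shrinkage |
|---|---|---|---|---|---|
| 2 | 3 | 13% | 31% | 1.22 | 39% |
| 3 | 5 | 10% | 17% | 1.44 | 28% |
| 2 | 5 | 1% | 7% | 1.83 | about 8% |

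With SD 2, a true difference of 1 degree becomes 0.65 (cut-off 3) or 0.95 (cut-off 5), and one of 3 degrees becomes 1.65 or 2.60. In every case computed, the difference moves toward zero and the losses are unequal between arms.

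**Step 5: effect on the planned statistic.** The widest distribution-free interval for a median, minimum to maximum, covers 1 − 2(0.5)^n: 99.2% at n = 8, 96.9% at n = 6 and 93.8% at n = 5. Three losses in one arm would leave no exact distribution-free 95% CI for that arm's median.

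**The case against.** **Removal is not stated.** A reader might infer that the plan removes these patients from the trial or the analysis. No section says so. The discontinuation section (2.4) names none of the three events, and eligibility is ticked only at screening, so the criteria might never operate. An analysis plan not shown may define the analysis set, and its absence here is not held against the article. This stands and limits the point to what follows if the stated rule is applied.

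**The items could be history.** The words about a background of an active septic process might be read as governing the rest of the list. Primary arthroplasty defeats that for the study hip. For a previous prosthesis on the other side the reading is possible but strained, since the Discussion treats the contralateral hip as not operated on.

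**Alignment is not truncated by definition.** A reader might infer a fixed cut on the outcome. The criterion has no threshold, may also cover the cup, and may mean gross malposition judged clinically. Table 1 also lists the alignment angle as a secondary objective, although Table 2 and section 2.14 make it primary. Overlap is supported; a known truncation is not.

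**Harms are not hidden.** A reader might infer that the arms would look safer than they are. Adverse events are recorded at every visit and described by group, with a 95% CI for the difference in serious events (2.19), and postoperative complications are collected (2.11). Nothing limits these to uncomplicated patients.

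**Who would judge is not stated.** The surgical team is unblinded, but no section assigns these criteria to it.

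**Sampling error is larger.** In the SD 3 scenario the bias is 2.00 − 1.44 = 0.56 degrees. The large-sample standard error of a difference in medians is 1.253 × 3 × √(2/8) = 1.88 degrees, so the bias is 0.56/1.88 = 0.30 standard errors. The trial is also an exploratory pilot with no confirmatory conclusion. Both lower the stakes; neither removes a bias that the wording invites.

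**Conclusion.** The point holds in conditional form. For the study hip, three criteria in section 2.2.2 cannot be assessed when eligibility is checked and can be met only after allocation. One of them is undefined and overlaps a primary outcome. If they are applied as written, the comparison is conditioned on outcome, at a cost of 12.5% of an arm per patient lost.

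The direction, toward no difference in alignment, rests on equal spread in the two arms and a cut-off symmetric about the femoral axis. The size is not computable from the document: for a true 2-degree difference, the assumed scenarios retain 1.22 to 1.83 degrees, a shrinkage of about 8% to 39%. No single figure in that range should be quoted as the effect. No size can be given for SPECT uptake.

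**What to change.** 1. Restrict section 2.2.2 to conditions that can be assessed before randomisation, and delete the three postoperative events from it.
2. State that all randomised patients are analysed by allocated group using all available data. Limiting the set to patients who received a stem would itself be a condition arising after randomisation.
3. Report misalignment by arm, with a stated definition and assessor, alongside the septic complications and periprosthetic fractures already captured as adverse events.
4. If an uncomplicated subset is wanted for SPECT uptake, label it a sensitivity analysis and give the number excluded per arm.

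Whether patients with such events continue to be scanned is a matter for the investigators.

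The cost is a wording change to the eligibility and analysis-population sections, with no extra patients. The small downside is some noisier uptake values after complications, which the sensitivity analysis would show.
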